## Abstract

**Background:**

Several observational studies have shown that exercise reduces the risk of cognitive decline; however, evidences from long-term, well-conducted, randomized controlled trials are scanty. The principal aim of this study is to verify whether a long-term program of multimodal supervised exercise improves the cognitive function and/or reduces the rate of cognitive decline in older adults at different degrees of risk for dementia.

**Methods/design:**

EPD is a parallel group, double-blind, randomized controlled trial. Community-dwelling volunteers aged 50 years or more are being recruited from different community centers and screened for eligibility. Enrolled subjects are being divided in 3 groups: a) without subjective or objective cognitive impairment, b) with subjective memory complaints, and c) with mild cognitive impairments. Participants in each group (at least 180) are being randomly assigned (1:1) to an experimental group, performing a supervised training including aerobic and resistance exercises of moderate/high intensity, or to a control group. Primary outcome will be 48-months changes in Mini Mental State Examinations. Secondary outcomes will be changes in several cognitive tests including a composite cognitive score. Time points will be at baseline, and at 6, 12, 24, 36 and 48 months. Statistical analysis will be done as intention to treat, complete case and mixed model analysis.

**Discussion:**

EPD is the first trial to examine the effects of a long exercise program (48 months) on cognitive performances. If successful, this trial may provide evidence for using long-term and multimodal exercise interventions for dementia prevention programs in the aging population.

**Trial registration:**

The study is registered at ClinicalTrials.gov with the code NCT02236416.

## Background

According with the report of the Alzheimer’s Disease International published in 2015, 46.8 million people are estimated to live with dementia worldwide, and this number might reach 131.5 million by 2050 [1]. Consequently, preventing and/or delaying cognitive impairment is a public health priority.

Alzheimer’s disease (AD) is the most common form of primary dementia and loss of episodic memory is often an early clinical symptom. The brain changes of AD may begin 20 or more years before symptoms appear [2], then identification of preclinical stages and preventive strategies to delay cognitive decline have become the focus of recent research. Several studies demonstrated that AD may be preceded by conditions known as subjective memory complaints (SMC) and/or mild cognitive impairment (MCI), that may be transitional stages between normal aging and dementia. SMC indicates a self-reported memory decline in the absence of pathological results on neuropsychological tests; it was estimated that elderly people with SMC have 2.7 times higher risk of developing dementia [3]. The estimated prevalence of MCI ranges from 10 to 20% with a rate of progression from MCI to dementia that variates from 5 to 20% per year depending on the examined population [4]. Furthermore, it has been calculated that if we could slow the progression to dementia in subjects at risk for just 12 months, in the 2050 we could have 9.2 million fewer cases of AD worldwide [5]. This delay in AD onset can represent a fundamental strategy, because nowadays AD is a fatal disease with no effective cure or treatment [6].

Despite the lack of therapies, several studies have shown that lifestyle modification and reduction of modifiable risk factor for AD offers a promising way of decreasing the risk of dementia [7, 8]. Physical inactivity is considered one of the seven main potentially modifiable risk factors for AD and explains approximately 13% (nearly 4.3 million) of AD cases worldwide [9]. However, some authors have reported that insufficient evidence exists to confirm the protective role of physical exercise in preventing AD onset [10]. The randomized controlled trial (RCT) investigating the effect of exercise on cognition did not provide definitive results due to the variation between study designs [11]. Two recent meta-analyses [12, 13] stated that the positive effects of exercise on cognition are driven by interventions that include aerobic exercise. Nevertheless, one of these two meta-analyses [13] concluded that methodological limitations of the included studies make the results interpretable with caution. Overall, the main limitations found in literature concerned the duration of the interventions that is usually lower than 12 months and the low standardization of the exercise protocol. Thus, well-designed RCT are recommendable and necessary [11, 12].

For these reasons, the aim of the present study is to verify if a 48-month program of supervised exercise reduces the rate of cognitive decline among older adults at risk of dementia. To the best of our knowledge, this RCT will represent the first study with such long duration.

## Methods

### Trial design

This study was named EPD (Exercise for the Prevention of Dementia). EPD study is designed as a phase 3, parallel group, double-blind, 1:1 RCT, conducted using the CONSORT statement (http://www.consort-statement.org/) as a framework for the development of methodology. The paper also adheres to the main aspects of the SPIRIT guidelines for reporting clinical trial study protocols. The flowchart of the study is reported in Fig. 1.

**Fig. 1 Fig1:**
[figure not shown]
Flowchart of the study

### Participants

Community-dwelling volunteers aged ≥ 50 years, with sedentary or normally-active lifestyle in accordance with the definition of Pate et al. [14], are being recruited from community centers for elderly in Campobasso, Italy. Recruitment methods include advertising, study presentations at community center, and word of mouth. Staggered enrollment of participants and relative data collection started in May 2011 and the estimated completion date should be May 2019.

Exclusion criteria include: a) short version of Geriatric Depression Scale (GDS) score > 6 due to the presence of clinically significant depression [15]; b) alcohol intake of more than 4 units/day; c) medical conditions that compromise survival, such as metastatic cancer, or limit exercise practice, such as severe cardiac failure; d) diagnosis of dementia according to International Statistical Classification of Diseases, 10th Revision (ICD-10) [16]; e) Mini- Mental State Examination (MMSE) age-education-adjusted score of less than 24 [17]; f) Clinical Dementia Rating (CDR) scale score of 1 or more [18]; g) inability to walk for 6 min without assistance [19]; h) use of drugs or other substance, or presence of a medical condition influencing the cognitive function. Eligible subjects are being divided into 3 category groups: A - without subjective or objective cognitive impairment; B - with SMC; and C - with MCI. Subjects in the category group A show a score < 25 at Memory Complaint Questionnaire (MAC-Q) [20], and a normal performance at neuropsychological test battery. Participants in the category group B show normal performance at neuropsychological test battery, including Rey’s Auditory Verbal Learning Test (RAVLT) and Prose Memory Test (PMT) [21], but a score ≥ 25 at MAC-Q. Participants in the category group C meet the International Working Group (IWG) diagnostic criteria on MCI [22], and show MMSE score ≥ 24, CDR score = 0.5 and pathological age-sex-education-adjusted scores at least one test of neuropsychological battery. For more clarity, a schematic representation of the groups is reported in Table 1.

**Table 1 Tab1:** Criteria for the participants’ categorization

Category groups	Criteria		
	MAC-Q score	Neuropsychological tests	MMSE and CDR scores
A Subjects without subjective or objective cognitive impairment	< 25	normal	• MMSE ≥24 • CDR = 0.0
B Subjects with SMC	≥25	normal	• MMSE ≥24 • CDR = 0.0
C Subjects with MCI	Any score	At least one pathological score	• MMSE ≥24 • CDR = 0.5

*SMC* Subjective Memory Complaints, *MCI* Mild Cognitive Impairment, *MAC-Q* Memory Complaint Questionnaire, *MMSE* Mini- Mental State Examination, *CDR* Clinical Dementia Rating

This study has been designed and it is being conducted in accordance with the principles of the Declaration of Helsinki. It has been approved by the Local Ethics Committee and the Agency for Public Health of Molise Region, and was registered at ClinicalTrials.gov (NCT02236416). A written informed consent is required for all participants and the corresponding personal data are treated according with the Italian Legislative Decree 30 June 2003, n. 196 “Code concerning the protection of personal data”. The administration of the informed contents was performed by the researchers of the study.

### Baseline and successive assessments

The potential eligible participants are invited at the Center for Research and Training in Medicine of Aging of the University of Molise to an in-person assessment that includes: 1) general conditions and health status, 2) neurocognitive performances, and 3) physical fitness levels. The three assessments are performed individually in 3 non-consecutive days. The baseline assessments were also used to screen the participants to exclude those that meet exclusion criteria, and to categorize them in A, B or C category groups. Successively, the assessment sessions are repeated at 6, 12, 24, 36 and 48 months to evaluate the differences among time-points.

#### General conditions and health status assessment

The following information are collected: socio-demographic data, that is age, gender, ethnicity, income, instruction level and marital status; behaviors (e.g. smoking, alcohol consumption); medical history and clinical conditions, evaluated with a pre-defined check-list; anthropometric measures, that is weight, height, body mass index, waist circumference; blood pressure (checked with calibrated mercury sphygmomanometers); blood sample analysis (for assessing the cardiovascular risk), that is glucose, urea nitrogen, creatinine, total cholesterol, HDL and LDL cholesterol, triglycerides, transaminases, and complete blood count; and medications used.

The blood samples are collected after 12 h of fasting, between 8 and 10 am, and they are all analyzed in the central laboratory of the Local Public Health Institute.

Finally, in accordance with the recommendations proposed by the American Heart Association [23], participants with intermediate or high cardiovascular risk, following the classification of the ACSM [24], have to perform an ergometric test, in order to evaluate their effective eligibility for the proposed procedures.

#### Neurocognitive assessment

To measure the main cognitive functions of each participant, a neuropsychological test battery, administered by trained assessors in blind mode, is used. The battery consists of the tests described below.

*MMSE* for global cognitive assessment [17], *Frontal Assessment Battery (FAB)* for frontal lobe functions [25]; *Rey’s Auditory Verbal Learning Test (RAVLT)* [26] and *Prose Memory Test (PMT)* for learning and verbal memory [27]; *Attentive Matrices Test* for selective visual attention [27]; *Raven’s Progressive Matrices* for problem solving ability [28]; *Stroop Color Word Interference Test* [29] and *Trail Making Test (TMT) version A and B* [30] for cognitive flexibility and ability to shifting; and *Copying of Drawings* with and without landmarks for visual-spatial ability [31].

Furthermore, 15-item *Geriatric Depression Scale (GDS)* [15] and the *Short-form Health Survey (SF-36)* [32] were used to assess symptoms of depression and life quality respectively. The *MAC-Q* [20] was used for the subjective assessment of the memory complaint. The tests of the neuropsychological battery are administered in a fixed order with alternative form [33].

#### Physical fitness level assessment

The level of physical activity of each participant is assessed with the Physical Activity scale for the Elderly (PASE) [34] that is a questionnaire consisting of 12 items quantifying physical activity performed during leisure, household, and/or occupational activities.

The overall physical condition is evaluated by the American Alliance for Health, Physical Education, Recreation, and Dance (AAHPERD) fitness battery [35], including the following tests: *Sit and Reach Test*, for measuring flexibility of the trunk/leg; *Agility Test*, for testing agility and dynamic balance; *Soda Pop Test*, for the assessment of the oculo-manul coordination; *Arm Curl Test*, that measures muscular strength/endurance of the upper body; *Six minutes walking test (*replacing the half-mile walking ability test*)* for the assessment of the cardiorespiratory fitness.

### Procedures

After the baseline assessments, the subjects in each category group (A, B and C) is identified by a progressive number and randomly assigned in a ratio of 1:1 to experimental or control group, using a list of random numbers generated by a statistical software (SPSS). The list was kept in a sealed envelope and a researcher, not directly involved in the recruitment and in the evaluation of the participants, assigned the allocation numbers.

#### Experimental group (EG)

Participants randomized to the experimental group are asked to participate in one-hour exercise classes, three times a week, for 48 months. The classes, with a maximum of 12 participants, are organized in the rooms of the University Sports Center of the University of Molise and are led by experienced instructors trained to supply the same program in each class. Exercise program is individualized based on physical function, physical fitness level, health status, and exercise responses.

Exercise intensity are measured according to the Borg’s Rating of Perceived Exertion (RPE), a 6-to-20 points scale [36] on which a score < 11 is considered an effort equal to a light exercise, 12–13 to a moderate exercise, and 14–17 to a vigorous exercise [37]. The RPE scales were extensively used and demonstrate moderate to strong validity compared with other measures of cardiorespiratory exercise intensity, such as percent of the maximal oxygen uptake (% VO_2max_), percent of the maximum heart rate (% HRmax), and blood lactate concentrations [37]. The training program and RPE system were chosen and designed to be easily reproducible at home, to promote a physical active life-style also after the end of the study.

The exercise programs offer a wide variety of exercises including aerobic, strengthening/endurance (resistance), and flexibility (stretching) exercises. Each session consists of a warm-up, aerobic, resistance, cool-down and stretching phase.

The *warm up phase* lasts 5–10 min and consists of light-to-moderate intensity (RPE 10–12) aerobic activity. During this phase, fitness ergometers, such as treadmill and/or stationary bicycle, or walking/jogging activities are used to activate the biggest muscular groups. Then, the *aerobic phase* lasting 15–20 min is performed by treadmill, stationary bike, arm-cycle ergometer and/or running. Duration and intensity of exercise are gradual over time, starting with multiple bouts (< 2 min) of light to moderate intensity (RPE max 12–13) exercises up to two 10-min bouts of moderate to vigorous exercise (RPE max 16–17), after several week of training. Subsequently, the *resistance phase,* lasting 20–25 min and involving the principal muscular groups of limbs and trunk, is carried out by bodyweight exercises (calisthenics) and dumbbells up to 2 kg. Duration and intensity are also progressive over time, starting with 2 series of 10 repetitions (RPE max 11–12) up to 6 series of 20 fast repetitions (RPE max 14–16), for each muscular group. Finally, the *stretching phase*, lasting less than 10 min, consists in flexibility exercises for each major muscle/tendon groups. Participants are invited to stretch to the point of feeling tightness or slight discomfort, hold a static stretch for 20–30 s and repeat the exercise 2–3 times for each muscle/tendon group.

The instructors monitor exercise intensity during all sessions taking care of the needs of the participants.

Participants with a number of absences > 50% are considered not adherent to the training.

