### Sample size calculation

Sample size calculations were based on the findings of previous studies and were performed separately for each category group. For heathy group, considering that MMSE scores decline 0.3 points in 4 years, we considered 0.6 points the minimal clinically important difference and used a Standard Deviation (SD) of 1.2 [38]. For SMC group, since that annual decline in MMSE score vary between 0.46 and 1.32 and that SD may vary between 1.48 and 2.6 [39], we considered 1.3 points the minimal clinically important difference and used a SD of 2.6. For MCI group, considering that the annual decline in MMSE score vary between 0.1 and 1.1 [40] and that SD may vary between 0.3 and 3.2 [41], we considered 1.6 points the minimal clinically important difference and used a SD of 3.2. Considering the percentage of drop-outs in previous similar studies and the length of the present study, we assumed a 30% attrition rate. Using an α level of less than 0.05, 90 participants per arm group will guarantee a power of 0.80.

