### Statistical analysis

Data will be analysed using the SPSS statistical software package (IBM, v.20.0, Chicago, IL, USA). Variables will be examined for outliers and extreme values by means of box and normal quantile-quantile plots, Shapiro-Wilk’s and Kolmogorov-Smirnov’s tests. When normal distribution cannot be accepted, the transformed variable (square, square root, logarithmic, reciprocal of square root or reciprocal transformations) will be reviewed. For normally distributed continuous variables, arithmetic means and SDs will be calculated, while for not normally distributed continuous variables, median, 25th and 75th percentiles will be calculated, according to the shaped distributions of two groups, as assessed by visual inspection of population pyramids. Sampling homogeneity (or baseline differences between groups) will be examined by means of chi-square (χ^2^) for categorical variables, independent-samples t-test for normally distributed variables and Mann-Whitney U test for not normally distributed variables. Differences between groups (experimental group vs. control group) and changes in the cognitive performance during the trial will be evaluated by means of Repeated Measures Analysis of Covariance (RM-ANCOVA) in the intention to-treat and complete-case analyzes, or with Linear Mixed Model analysis (LMM). The evaluations in the different time-points will be considered as the within-subjects factor whereas the two groups will be considered as between factor. Age, education level and gender will be included as covariates. The assumptions of equality of variances and sphericity will be assessed by means of Levene’s test and Mauchly’s test, respectively. The Greenhouse-Geisser or the Huynh-Feldt correction will be applied if the assumption of sphericity will be violated. Post-hoc independent-samples t-test will be performed to detect significant differences among trial conditions.

A *p*-value < 0.05 will be considered statistically significant.

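### The stated analysis and the 90 per arm make no allowance for clustering by exercise class in the experimental arm; the effect runs from negligible to moderate, depending on an ICC and class make-up that are not given

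*Protocol article*

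**What the plan says.** Under Procedures, individuals are randomised 1:1 within each of the category groups A, B and C. Under Experimental group (EG), those allocated to exercise attend one-hour sessions three times a week for 48 months: "The classes, with a maximum of 12 participants, are organized in the rooms of the University Sports Center". The same paragraph says that instructors are trained to deliver one common programme and that exercise is tailored to the individual. Under Control group (CG), controls keep their usual lifestyle or usual light activity, and no trial classes are described for them.

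Statistical analysis names repeated-measures ANCOVA or a linear mixed model. Time is the within-subject factor and "the two groups will be considered as between factor"; age, education and gender are covariates, and independent-samples t-tests follow. No class or instructor term appears.

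Sample size calculation works separately for each category group. It gives a difference, an SD, an attrition rate, an alpha and a power, and ends: "Using an α level of less than 0.05, 90 participants per arm group will guarantee a power of 0.80". It mentions neither an ICC nor a design effect.

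**The concern.** This is an individually randomised trial with group-delivered treatment in one arm, that is, a partially nested design. Classmates share an instructor, a room, an attendance climate and social contact for up to four years. Any of these can make their outcomes more alike than those of participants in different classes. If so, the variance of the experimental-arm mean is larger than an independent-participant analysis assumes. The confidence interval for the MMSE difference is then too narrow, the test rejects a true null more often than 5% of the time, and a valid analysis has less power than stated. Blinded outcome assessment does not remove correlation that arises from shared treatment.

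**Working it through.** **Inputs from Sample size calculation.** Group A: "we considered 0.6 points the minimal clinically important difference and used a Standard Deviation (SD) of 1.2". Group B: "we considered 1.3 points the minimal clinically important difference and used a SD of 2.6". Group C: "we considered 1.6 points the minimal clinically important difference and used a SD of 3.2". The standardised difference is 0.6/1.2 = 1.3/2.6 = 1.6/3.2 = 0.5 in each. Attrition: "we assumed a 30% attrition rate". Alpha is 0.05, taken as two-sided because that reproduces the plan's figure; one-sided gives 50 per arm before attrition and does not. Power is 0.80.

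**Reproducing the plan's figure.** n per arm = 2(1.960 + 0.842)²/0.5² = 62.8, so 63. Then 63/(1 − 0.30) = 90, an exact match. Power with 63 per arm is Φ(0.5/√(2/63) − 1.96) = 0.801 (0.795 from the t distribution). At the assumed attrition, 90 therefore contains no allowance for clustering.

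**Adding clustering in the experimental arm only.** For m analysed participants per class:

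- Design effect, experimental arm: DE = 1 + (m − 1) × ICC; control arm: 1.
- True SE of the difference, in SD units: √((DE + 1)/63). SE under independence: √(2/63). Ratio R = √((DE + 1)/2).
- Power of a valid analysis: Φ(0.5/√((DE + 1)/63) − 1.96).
- Actual two-sided alpha of the independent analysis: 2(1 − Φ(1.96/R)).

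**Assumptions.** The ICC is not in the protocol and is taken as 0.01 to 0.05. Three values of m are used: 12 (the stated maximum), 8.4 (12 less 30% attrition) and 4 (classes that mix A, B and C, so that about a third of a class of 12 falls in each comparison). Classes are treated as fixed, equal in size and non-overlapping, and the total SD as equal in both arms.

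*Example:* m = 8.4, ICC = 0.05. DE = 1 + 7.4 × 0.05 = 1.37. True SE = √(2.37/63) = 0.194. Power = Φ(0.5/0.194 − 1.96) = 0.732. R = √(2.37/2) = 1.089. Alpha = 2(1 − Φ(1.96/1.089)) = 0.072.

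| m | ICC | DE | R | Power | Actual alpha |
|---|---|---|---|---|---|
| 12 | 0.01 | 1.11 | 1.027 | 0.780 | 0.056 |
| 12 | 0.02 | 1.22 | 1.054 | 0.759 | 0.063 |
| 12 | 0.05 | 1.55 | 1.129 | 0.700 | 0.083 |
| 8.4 | 0.01 | 1.074 | 1.018 | 0.787 | 0.054 |
| 8.4 | 0.02 | 1.148 | 1.036 | 0.773 | 0.059 |
| 8.4 | 0.05 | 1.37 | 1.089 | 0.732 | 0.072 |
| 4 | 0.01 | 1.03 | 1.007 | 0.795 | 0.052 |
| 4 | 0.02 | 1.06 | 1.015 | 0.790 | 0.054 |
| 4 | 0.05 | 1.15 | 1.037 | 0.772 | 0.059 |

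At ICC = 0 every row returns to 0.801 and 0.050.

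**Two checks on these figures.**

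- *Attrition.* If all 90 per arm are analysed, power without clustering is Φ(0.5/√(2/90) − 1.96) = 0.918. With m = 12 and ICC 0.05 it is Φ(0.5/√(2.55/90) − 1.96) = 0.84. R does not depend on n, so alpha in that case stays at 0.083.
- *Few classes.* The table uses the normal approximation, which flatters power when the class variance is estimated. With m = 8.4 and 63/8.4 = 7.5 classes, Satterthwaite df = (1 + DE)²/(DE²/6.5 + 1/62). At ICC 0.05 this is 2.37²/(1.37²/6.5 + 1/62) = 18.4. Power is then about 0.75, 0.73 and 0.69 at ICC 0.01, 0.02 and 0.05.

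**The case against.** The strongest reply is that none of the quantities that set the size of the effect is in the protocol. The ICC is not given, and a common programme, individual tailoring and blinded assessors could keep it small. The protocol does not say whether classes are formed within category groups. If they mix A, B and C, the effect at ICC up to 0.02 is trivial. Nor does it say that membership is stable: enrolment is staggered, training lasts 48 months and 30% are expected to leave, so the fixed-class formula is an approximation. Controls may also exercise in groups outside the trial, which the protocol neither states nor excludes. Finally, an article may leave the random-effect structure of a mixed model to a fuller plan.

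Most of this stands as a limit on size. It does not remove the point. The factors that reduce the ICC give no reason to set it to exactly zero, which is what the stated N does. Mixing and turnover lower the effective class size but leave some correlation. A fuller plan could add a class term to the mixed model, but the repeated-measures ANCOVA and t-tests that the article does specify treat participants as independent, and the stated N has no room for clustering at 30% attrition.

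A reader might infer that the standard errors are certainly too small, or that the trial is underpowered whatever happens. The documents support neither: both depend on a positive ICC, and the power loss also depends on attrition reaching 30%. A larger ICC, such as 0.10, would give more striking figures, but nothing in the protocol points to one.

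**Conclusion.** The point holds in conditional form. Treatment is delivered in classes in one arm, while the stated model and the stated N ignore this. If the within-class ICC is positive, standard errors are understated and power at 30% attrition is below the independence value of 0.801. Over an assumed ICC of 0.01 to 0.05 with 63 completers per arm, power falls by between less than 1 percentage point (0.795; about 4 per class, ICC 0.01) and about 10 points (0.70; 12 per class, ICC 0.05). Actual alpha lies between about 0.052 and 0.083. Better retention can restore the power but not the type I error. What the protocol fixes badly is the unqualified claim that "90 participants per arm group will guarantee a power of 0.80", together with a model that has no place for class.

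**What to change.** In Statistical analysis, make the linear mixed model, already listed as an option, the main model. Add a random class effect that applies to the experimental arm only, with controls as singletons, and use Satterthwaite or Kenward-Roger degrees of freedom. Code class as the one first assigned, and repeat the analysis with the class attended most as a sensitivity analysis, since membership may change over 48 months. In Sample size calculation, replace the unconditional power statement with the power over a stated ICC range such as 0.01 to 0.05, and say whether classes mix the category groups.

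The cost is one more variance term, slightly wider intervals and a less favourable stated power; no extra participants are asked for. With few classes the class variance will be estimated imprecisely. Class identity must also be recoverable from class records: the rule on absences implies that attendance is counted, but the protocol does not say that the class attended is recorded.
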